# Study Enrollment and Withdrawal

This study will enroll 20 healthy adults between 18-45 years of age. Both females and males will be eligible to enroll in the study. No restrictions will apply for ethnic or racial categories. The expected population to be enrolled may include all Australian racial categories, such as Australian White, Australian Indian, Australian Asian, Australian Aborigines or Torres Strait Islanders. This study will be conducted at Q-Pharm Pty. Ltd, Brisbane Australia. Q-Pharm is an independently registered Company that conducts Phase I clinical trials. It is co-located on the campus of the Royal Brisbane and Women’s Hospital (RBWH) and QIMR. Q-Pharm also offers services for participant recruitment for clinical studies from a variety of sources. Prior to their use, all advertisements used for recruitment of the participants in the study will be approved by the ethics committees of all institutions concerned. The enrollment of participants in the study will be performed in accordance with the principles of the ICH E6 Good Clinical Practice [3]. Screening consent will be obtained from each participant to collect the baseline specifications that will indicate the suitability of the participants for inclusion in this study. Once the suitability of the participants is confirmed at the screening visit, consent will be obtained from each participant to enroll into the interventional part of this study. Alternates may also be identified and held in reserve. The reserve participants will be asked to attend the clinic on Day 0, but they will take a part in the study if one or more participants withdraw before the first injection of the study vaccine.

## Participant Inclusion Criteria

All participants in the clinical study must meet all of the following inclusion criteria to participate in this study:

• Able to understand the purpose and the procedures involved in this study and sign the informed consent form;

• Male or non-pregnant female adults, 18-45 years of age inclusive;

• Non smokers and in good general health, as determined by screening evaluation, no greater than 28 days before the first dose in the form of medical history, clinical laboratory tests and physical examination;

• Normal Electrocardiogram (ECG);

• Echocardiogram (ECHO) that is normal or with findings that are considered trivial and clinically insignificant such as:

- 'Clinically insignificant/trivial mitral regurgitation (EROA of <10mm2, quantified as described in Appendix H) ;

• Women must agree not to become pregnant for the first 180 days of the trial. If they are sexually active, they must use an effective method of birth control, e.g. insertable, injectable, transdermal, or combination oral contraceptive approved by the US FDA or TGA combined with a barrier contraceptive and have negative results on a serum or urine pregnancy test done before administration of study medication;

• Intention to reside in the geographical area for next 12 months and not intending to travel overseas for at least 30 days following the last study vaccine administration;

• Agree not to participate in any other clinical trial during the trial;

• Agree not to donate blood for the first 180 days of the trial;

• Agree to restrain from intensive physical exercise i.e. exercise that varies significantly from an every day exercise routine, 3 days before and after (± 3 days) administration of each dose, including each interim visit for blood sample collection.

## Participant Exclusion Criteria

Any potential participants meeting any of the following criteria will be excluded from the study:

• Personal or family history of post-streptococcal disease (rheumatic fever or glomerulonephritis), or collagen-vascular disease;

• Has evidence of increased cardiovascular disease risk (defined as >10%, 5 year risk) as determined by the method of Gaziano et al., (36). Risk factors include sex, age, systolic blood pressure (mm Hg), smoking status, body mass index (BMI, kg/m2), reported diabetes status and blood pressure;

• Clinical diagnosis or evidence of recent group A streptococcal infection as measured by anti-streptolysin O or anti-DNase B levels exceeding 200 units;

• Positive group A streptococcus throat culture at screening visit or positive rapid antigen test result on day of study product administration;

• Evidence of multiple past group A streptococcus infections as measured by anti-J8 antibodies levels > 3 Standard Deviations above background Optical Density;

• Presence of significant acute infections requiring systemic antibiotic treatment within the 14 days prior to each product administration;

• Pregnant or breast feeding (all women will have a negative pregnancy test result prior to each study product administered);

• Immunized or intent to immunize with any vaccine or investigational agents within 30 days prior to enrollment through to 30 days following the last study vaccine administration, with the exception of licensed inactivated influenza vaccines;

• Receipt of diphtheria toxoid containing vaccine within the previous 5 years (such as DTP, Hepatitis A, Boostrix, Adacel or Menactra);

• Past significant reaction following any previous vaccination;

• History of hypersensitivity to any diphtheria toxoid containing vaccine;

• Presence of acute infectious disease or fever (e.g., sub-lingual temperature  38.5°C) within the five days prior to study product administration;

• Presence of current or suspected serious chronic diseases such as cardiac or autoimmune disease (HIV or other immunodeficiencies), insulin dependent diabetes, progressive neurological disease, severe malnutrition, acute or progressive hepatic disease, acute or progressive renal disease, psoriasis, rheumatoid arthritis, asthma, epilepsy or obsessive compulsive disorder, skin carcinoma excluding non spreadable skin cancers such as basal cell and squamous cell carcinoma;

• Evidence and any history of leukaemia, lymphoma or neoplasm;

• Presence or suspicion of impaired immune system function. Currently receiving or having within the past three years received immunosuppressive therapy, including systemic steroids, ACTH or inhaled steroids in dosages that are associated with hypothalamic-pituitary-adrenal axis suppression, such as 1mg/kg/day of prednisone or its equivalent or chronic use of inhaled high potency corticosteroids [budesonide 800 µg per day or fluticasone 750 µg];

• Received blood, blood products or a parenteral immunoglobulin preparation in the past 12 weeks;

• Evidence of bleeding diathesis or any condition that may be associated with a prolonged bleeding time;

• Known inherited genetic anomaly (known as cytogenic disorders) e.g., Down’s syndrome;

• Evidence of any condition that, in the opinion of the clinical investigator, might interfere with the evaluation of the study objectives or pose excessive risks to participants;

• Findings of definite, probable or possible rheumatic heart disease (RHD), definite or probable acute rheumatic fever (ARF) as defined in appendix F [35];

• Echocardiographic findings such as:

- - Cardiac Chambers: left ventricular dilatation (based on LV diameter > reference ranges for LV end diastolic diameter (LVEDd) indexed for body surface area (Females 24-32 mm/sqm; Males 22-31mm/sqm);
  - left ventricular dysfunction (Ejection Fraction < 50%; left ventricular hypertrophy (LV wall thickness > 11mm); Right ventricular dysfunction or dilatation (Subjective assessment);
  - Cardiac Valves/Haemodynamic Findings: Clinically significant mitral regurgitation defined: at the discretion of the cardiologist and/or effective regurgitant orifice area of 10mm2; Any degree of valvular stenosis or left ventricular outflow tract obstruction; Pulmonary hypertension (defined as an estimated right ventricular systolic pressure of >40 mmHg, calculated using the peak tricuspid regurgitant jet velocity method);
  - Any aortic regurgitation;
- Pericardium: greater than trivial pericardial fluid (trivial defined as < 5mm and not circumferential);
- Pre-existing significant structural valve disease (for example, but not limited to bicuspid aortic valve regardless of haemodynamic effect, mitral valve prolapse regardless of severity of regurgitation, pulmonary stenosis);
- Other significant congenital lesions (for example, but not limited to aortic coarctation, septal defect, excluding patent foramen ovale (NOTE: findings considered normal developmental variation, specifically including patient foramen ovale and prominent Eustachian valve will not be considered exclusion criteria;

• Clinical or sub-clinical acute post-streptococcal glomerulonephritis (APSGN), as defined in appendix F [35];

• Clinical significant abnormal laboratory results e.g., CBC with differential and platelets, AST, ALT, total bilirubin, urea, creatinine, electrolytes (including sodium, potassium, chloride and bicarbonate), troponin T, C-reactive protein, C3 complement, Antinuclear antibodies (>320 titer or >160 with homogeneous pattern) and anti-cyclic citrullinated peptide antibodies (Anti-CCP antibody);

- The participant has a diagnosis of schizophrenia, bi-polar disease, or other severe (disabling) chronic psychiatric diagnosis;
- The participant has been hospitalized within the past 5 years prior to enrollment for psychiatric illness, history of suicide attempt or confinement for danger to self or others;
- The participant is receiving psychiatric drugs1. Participants who are receiving a single antidepressant drug and are stable for at least 3 months prior to enrollment without decompensating are allowed enrollment into the study;

2 1aripiprazole, clozapine, ziprasidone, haloperidol, molindone, loxapine, thioridazine, thiothixene, pimozide, fluphenazine, risperidone, mesoridazine, quetiapine, trifluoperazine, trifluopromazine, chlorprothixene, chlorpromazine, perphenazine, olanzapine, carbamazepine, divalproex sodium, lithium carbonate or lithium citrate.

- The participant has a history of alcohol or drug abuse in the 5 years prior to enrollment.

## Treatment Assignment Procedures

### Randomization Procedures

Enrollment will be done by Q-Pharm. The randomization code will be included in the enrollment module for the trial. The randomization code will link the vial allocation number to the treatment assignment. Each subject enrolled in the trial is assigned to a vial allocation number after demographic and eligibility data have been entered into the system. The code list for emergency unblinding purposes will be kept in a secure place at the clinical site.

### Masking Procedures

In this trial all personnel from QIMR and Q-Pharm will be blinded to the randomization scheme, except for the member(s) of the study team at Q-Pharm who are responsible for preparing and administration of the vaccine and saline as well as the statistician supporting the SMC (as necessary).

In a location in the trial clinic where blinded study personnel are not present, the unblinded study pharmacist will prepare that study product for injection and an unblinded nurse will check the dose and administer the product. To maintain the blind, the study participants will place their arms on which the vaccine will be administered under a curtain barrier, thus they will not know whether study product or control is being administered.

Documentation will be made in the study record indicating the date and time of study product administration. The participant, the study personnel who perform study assessments after product administration, investigators, data entry personnel at the sites, and laboratory personnel performing immunologic assays will also be blinded to treatment assignment.

The unblinded member of the team will be instructed not to share treatment code information with the participant, QIMR staff, or the Q-Pharm study team staff at the clinical site. In addition, the unblinded staff will not perform any other study related duties apart from the preparation and administration of the study product.

### Termination of Study

The study may be terminated before of after continuation with the vaccine second dose:

- If serious safety concerns are identified by the Clinical Investigator, Program Investigator, QIMR-HREC, the TGA sponsor QIMR or the appointed Safety Monitoring Committee.

- In the event that the TGA sponsor (QIMR) chooses to discontinue or terminate the study, appropriate notification will be given to the investigator.
- If the study is terminated, participants who have received the investigational product will be followed for safety assessments as described in the Section on Early Subject Discontinuation.

### Reasons for Withdrawal

A participant will not receive further study product if unexpected serious clinical adverse event (SAE), an illness or medical condition, or a situation occurs such that in opinion of the Clinical Investigator, continued receipt of vaccinations would not be in the best interest of that person. Participants may voluntarily withdraw from receipt of future product administration and/or follow-up at any time.

### Handling of Withdrawals

If the participant is withdrawn from the study procedures or follow-up for any reason, with the participant’s permission, medical care will be provided for any SAEs that might have had occurred during the individual participation in the study until the symptoms of any SAEs are resolved and the participant’s condition becomes stable. If withdrawal from further product administration occurs, if willing the participant will be asked to continue the scheduled evaluations and to complete the early termination evaluation as described in section 7.6.

# Study Intervention/Investigational Product

## Study Product Description

The antigen component in the proposed vaccine candidate is an acetylated synthetic peptide (AcJ8) conjugated to diphtheria toxoid (D) carrier molecule. The J8 peptide is synthesized on a solid phase resin purified using preparative HPLC, acetylated (AcJ8) and then conjugated to diphtheria toxoid (D) carrier molecule. The AcJ8-D conjugate is adsorbed onto alum (2% Aluminum hydroxide, Alhydrogel). The vaccine formulation also contains phosphate as a pH stabilizer in an isotonic 0.9% sodium chloride solution. The vaccine formulation is a sterile, white, homogeneous suspension intended for intramuscular injection that will be supplied in single dose vials.

### Acquisition

The vials containing the vaccine candidate will be stored at Q-Gen prior to initiation of the study.

### Formulation, Packaging, and Labeling

Each 0.5 mL dose of the vaccine candidate contains approximately 15 μg of AcJ8 peptide, 35 μg of diphtheria toxoid and between 315-715 μg elemental aluminum as determined by assay.

The vaccine will be aliquoted in clear type I glass vials. All vials will contain sufficient amount of formulated vaccine for a single dose of 0.5 mL volume. The vials containing the aliquoted vaccine formulation will be labeled in accordance to the GMP guidelines.

The saline control is a sterile 0.9% sodium chloride solution and it will be administered in the participants randomized to receive placebo. Saline will be sourced by Q-Pharm in 2 mL ampoules. Each vial will be utilized for a single dose.

### Product Storage and Stability

The vaccine candidate will be aliquoted in clear Type I glass vials in a total volume of 0.7mL ± 5%, which is approximately 40% overfill of the amount required for administration. This amount will be sufficient to aliquot a single dose injection of 0.5mL. All vials containing the aliquoted vaccine candidate will be stored at 5°C ± 3°C, protected from light in the provided packages.

The content in the vaccine candidate vials MUST NOT BE FROZEN. Any vials containing frozen vaccine contents must be discarded.

The saline vials will be handled and stored at room temperature as per package insert.

## Dosage, Preparation and Administration of Study Intervention/Investigational Product

**Study Intervention vaccine**

Preparation:

The vaccine formulation is ready-to-use suspension. The vaccine suspension must be mixed well by gently inverting the vial to resuspend any deposits that might form during the storage. After mixing, the vaccine formulation has a whitish color. Prior to administration the vaccine suspension must be examined visually. If any discoloration or particulate is observed, the vial should be discarded. The vaccine should be kept on cold until it is administered.

Administration:

Each vial contains a sufficient quantity of vaccine suspension for a single injection. 0.5mL of the vaccine suspension from each vial is removed for a single dose. The first dose will be administrated intramuscularly (I.M.) in the deltoid region of the non-dominant arm or the arm opposite that used for blood draw. The second dose will be administrated in the alternate arm.

Dosage:

Each study participant randomized to receive the treatment will receive two injections at 8 weeks intervals.

**Saline**

Preparation:

Each dose consists of ready-to-use sterile 0.9% sodium chloride solution. Before use, the saline vial will be inspected to verify the labeling, that the vial is intact and contains a clear liquid solution. The saline vial will be discarded if the contents of the vial appear otherwise. Each vial is for use in a single participant only, and any residue will be discarded.

Administration:

The saline control will be administrated as a single 0.5 mL I.M. injection in the deltoid region of the non-dominant arm or the arm opposite that used for blood draw. The second dose will be administrated in the alternate arm.

Dosage:

The proposed dosage of the saline control in this study is 2 injections at 0.5mL volume at 8 week intervals.

## Accountability Procedures

Q-Pharm will request shipment of the vaccine candidate from Q-Gen prior to the initiation of the study, when the approval has been obtained from the QIMR - HREC Ethics Committee. The vials containing the saline control will be supplied by Q-Pharm. Vials containing the vaccine candidate and the saline control will be inventoried prior to the beginning of study enrollment on study accountability logs in regards to condition upon receipt, vial quantities, formulation/type of study product, lot and vial numbers. The Clinical Investigator (CI) or qualified study person designated by the CI will ensure that the received study products are the specified formulation. All vials will be placed into a locked temperature monitored refrigerator (5°C ± 3°C) protected from light until completion of the trial. Each dose of study vaccine or the saline control used or wasted will be accounted for in writing on the study accountability log at the time of the removal of the product from storage.

The unblinded study staff member who will prepare the study product will be responsible for maintaining accurate records in all the study accountability logs, as well ensuring that the vaccine vials are used in accordance with the protocol. Study products and study accountability logs will be available to QIMR or QIMR’s representative as part of the study monitoring procedures.

At the completion of the study, a clinical monitor will review final accountability records and QIMR will provide instruction for the used vials and the unused study products. The vials will be returned to the TGA sponsor (QIMR) or will be destroyed according to the standard process at the clinical site.

## Concomitant Medications/Treatments

Concomitant medications/treatments will be recorded during the 0-7 days following each dose and at the scheduled study visits (see Appendix A) and collected surrounding adverse events/serious adverse events. This documentation will include any prescription or nonprescription drug or other treatment. The name of the medication, start and stop dates of treatment, total daily dose, route of administration and indication will be recorded on the source documents.

Permitted concomitant medications:

- These medications include licensed hormonal contraceptives, antihistamines and decongestants for seasonal allergies, non-steroidal anti-inflammatory drugs, (e.g., ibuprofen), non-narcotic analgesics (e.g., paracetamol/acetaminophen) and antibiotics as medically indicated.

At each of the scheduled visits circumstances that could potentially interfere with the vaccine-induced immunity will also be checked for. These circumstances include:

1. Use of any investigational drug or investigational vaccine other than the study vaccine during the study period.

2. Administration of licensed vaccines within 30 days prior to screening and enrollment through to 30 days following the last study vaccine administration, with the exception of licensed inactivated influenza vaccines.

3. Administration of immunosuppressants or other immune-modifying drugs (as listed in the exclusion criteria)

4. Administration of immunoglobulins and/or any blood products up to 28 days after the last dose of vaccine.

5. Antibiotics prescribed for streptococcal throat infection.

If any of the participants require medications/treatments that are listed as exclusion criteria, the participant will be excluded from receiving further doses of the vaccine and will not be included in the immunogenicity evaluations. However, the participant will be encouraged to continue the scheduled follow-up visits and remain in the study for safety evaluation for doses already received.

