### Secondary Outcome Measures

• The production and the titer of the vaccine specific antibodies of the baseline titer after study product administration will be determined using ELISA. The presence of vaccine-specific antibodies in all participants in the study will be monitored and the titer of the vaccine specific antibodies after each dose of the vaccine candidate will be measured to investigate the relationship between the doses administered and the titer of vaccine-specific antibodies.

• The bactericidal activity of the induced antibodies against different standard reference strains of group A streptococcus such as M1, M6 and 88/30 (Australian clinical isolate) will also be assessed.

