**Day 56 ± 5 (Day of Dose 2)**

1. Ensure that an approval has been granted from SMC to proceed with the second study product administration.

2. Review inclusion/exclusion criteria.

3. Review medical history for any change in status from last study visit.

4. Review any acute complaints/adverse events/serious adverse events.

5. Review concomitant medications. If the participant has received an antibiotic treatment within 14 days prior to this administration, at discretion of the CI the participant may be withdrawn from the study or the administration of the second dose rescheduled within the allowed window for administration of the dose.

6. Record baseline symptoms and vital signs. If the participant is febrile (temperature >38°C [>100.4F] or has an acute illness, the study product administration must be rescheduled within the allowed window for administration of the dose.

7. Obtain a throat swab and conduct a rapid antigen test for group A streptococci.

8. Obtain a urine sample from all female participants for -HCG testing. Ensure that the testing is negative before study product administration.

9. Perform breath alcohol test and urine drug screen.

10. Collect urine for urinalysis and blood for hematology, biochemistry and serology including, ASOT, α-DNase B and detection of α-J8 peptide vaccine specific antibodies and blood sample for quantitative cellular response as well as serum samples for α-DT antibodies and safety serum storage (refer to appendix D for tests required and blood volumes).

11. Targeted physical examination including cardiac auscultation. Particular attention to any elicited symptoms and signs consistent with rheumatic fever i.e. rash, arthalgia/arthritis (joint pain/swelling), renal angle tenderness and cardiovascular examination and movement disorder.

12. Administer the study product in the alternate arm from previous dose.

13. Observe for at least 30 minutes after study product administration to evaluate for immediate adverse reactions. Repeat vital signs after approximately of 30 minutes after study product administration, or at least prior to discharge. Record any immediate injection site reaction or systemic reactions if they occur.

14. Educate the participant during the post-study product administration waiting period on proper use of the thermometers and injection site reaction measurement aid. Discuss the signs and symptoms of potential adverse events (AEs).

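### Section 6.4 drops a participant from the immunogenicity evaluations once a listed medication is needed, with no date or sample limit, so results obtained before the medication can be lost

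*Protocol*

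**What the plan says.** The rule is in Protocol section 6.4, Concomitant Medications/Treatments. Its trigger is "If any of the participants require medications/treatments that are listed as exclusion criteria". Its consequence is that "the participant will be excluded from receiving further doses of the vaccine and will not be included in the immunogenicity evaluations". The participant is then encouraged to keep attending and to "remain in the study for safety evaluation for doses already received"; continued use for immunogenicity is not mentioned.

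The trigger is the exclusion list in section 5.2. Some treatments covered there or in section 6.4 have an end date: the general vaccine restriction runs to 30 days after the last study dose, and item 4 of section 6.4 limits immunoglobulins and blood products to 28 days after it. The immunosuppressive therapy criterion and the psychiatric drug criterion have no such end date.

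Section 11.10.1 undertakes to analyse every time point, with the focus on 28 days after the final dose (Day 84). Section 11.7 prefers point and interval estimates to tests.

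On antibiotics, section 6.4 permits "antibiotics as medically indicated", while item 5 of its list of potentially interfering circumstances names antibiotics for streptococcal throat infection and attaches no consequence. Section 5.2 excludes "Presence of significant acute infections requiring systemic antibiotic treatment within the 14 days prior to each product administration". For antibiotic treatment within 14 days before Dose 2, section 7.3 says that, at the investigator's discretion, "the participant may be withdrawn from the study or the administration of the second dose rescheduled within the allowed window".

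**The concern.** A treatment started after a blood sample was drawn cannot change what that sample measures. A rule that removes the whole participant therefore removes valid results together with any that may be compromised. Section 11.10.1 puts its weight on Day 84, yet scheduled visits run to Day 350, and section 6.4 has interfering circumstances checked at each of them. That leaves a long period in which a later prescription could cancel a completed Day 84 result.

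The exclusion also depends on what happens after randomisation. People who need an immunosuppressant or a psychiatric drug may differ from those who do not, so the remaining set may lean towards participants who stayed well. With 15 vaccine and 5 saline recipients, each person lost shows in the interval estimates.

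The antibiotic wording raises a second question. The same event shortly before Dose 2 can lead to removal under one section and to a rescheduled dose under another, so membership of the immunogenicity data set may turn on which section is followed.

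**Working it through.** **1. Plan figures.** The protocol states no power, SD, dropout rate or rate of listed medication, so there is no calculated figure to reproduce. The allocation is consistent: 15 + 5 = 20 and 15/5 = 3.

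**2. Samples affected.** From Day 0, anti-J8 samples fall on Days 0, 28, 56, 84, 180, 266 and 350 (sections 7.2 to 7.5). If the rule covers the whole participant:

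| Listed drug starts | Earlier samples lost | Day 84 lost? |
|---|---|---|
| Day 50 | 0, 28 (2 samples) | not yet taken; Dose 2 is stopped |
| Day 100 | 0, 28, 56, 84 (4) | yes |
| Day 300 | 0, 28, 56, 84, 180, 266 (6) | yes |

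Under a prospective reading none of these earlier samples is lost.

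**3. Which triggers can act late.** With Dose 2 on Day 56, the general vaccine limit ends at 56 + 30 = Day 86 and the blood-product limit at 56 + 28 = Day 84. These limits leave little room for a late trigger. The criteria without an end date are chiefly immunosuppressants and psychiatric drugs.

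**4. Precision.** The 95% CI half-width for a mean (for example of log concentration), in SD units, is t(0.975, n−1)/√n. The numbers lost are assumptions.

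| Arm | n | Calculation | Half-width (SD) | Change |
|---|---|---|---|---|
| Vaccine | 15 | 2.145/3.873 | 0.554 | reference |
| Vaccine | 14 | 2.160/3.742 | 0.577 | +4% |
| Vaccine | 12 | 2.201/3.464 | 0.635 | +15% |
| Saline | 5 | 2.776/2.236 | 1.242 | reference |
| Saline | 4 | 3.182/2.000 | 1.591 | +28% |

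If every vaccine recipient responds, the exact 95% lower bound for the response proportion is 0.025^(1/n): 78.2% at n=15 and 73.5% at n=12.

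**5. Chance of any loss.** If each participant independently has probability r of a triggering treatment, the chance of losing at least one of 15 is 1 − (1 − r)^15. This is 54% at r = 5% and 79% at r = 10%. Both values of r are assumptions.

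**6. Antibiotics before Dose 2.** Dose 2 is allowed on Day 56 ± 5, so no later than Day 61, and 61 − 14 = Day 47. Antibiotic treatment after Day 47 is still within 14 days on the last permitted day. Such a participant could be rescheduled and dosed under section 7.3, while section 5.2 read with section 6.4 stops dosing and removes the participant from immunogenicity. The sections do not say which governs.

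**The case against.** The strongest reply is that section 6.4 never orders earlier results to be deleted. A reader might infer that it does, because the exclusion is unqualified. But the sentence also stops further doses and is followed by continued safety follow-up, so it can mean no immunogenicity evaluation from that point on, or even apply only while doses remain. This stands in part: deletion follows from the literal wording but is not expressly stated. The text does not choose between the readings, and that choice decides whether a Day 84 result counts.

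Setting aside samples taken under an interfering treatment is also a recognised per-protocol approach, and someone stopped after Dose 1 has no two-dose response to report. This stands for samples taken after the treatment; it gives no reason to discard earlier ones. The statistical analysis plan may define analysis sets, but this exclusion is already fixed in the protocol.

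Three stronger readings are tempting and not supported:
- **A late diphtheria booster.** A reader might take this as the clearest example. The general vaccine restriction ends 30 days after the last dose, and the diphtheria criterion looks back over the previous 5 years, so neither clearly covers a booster on Day 300.
- **Contradiction with all-participant wording.** Section 3.2.2 says "The presence of vaccine-specific antibodies in all participants in the study will be monitored", and sections 8.2.2 and 11.10.1 describe assays on everyone's sera. These statements describe sampling and assay coverage, not an analysis set.
- **Antibiotics both permitted and excluded.** General permission for "antibiotics as medically indicated" is compatible with a restriction limited to 14 days before dosing. Only the handling at Dose 2 conflicts, and the effect of item 5 is unclear.

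Finally, the losses are assumed, immunogenicity is secondary, and all analyses are declared exploratory. That limits the weight of the point without removing it.

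**Conclusion.** The point holds as a flaw in a stated rule. Section 6.4 applies a post-randomisation exclusion to the participant, without a date or sample limit, and some of its triggers can act long after Day 84. As written, it can remove results that the treatment could not have affected, which sits badly with the undertaking in section 11.10.1 to analyse every time point.

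The size is moderate. For assumed losses of one to three vaccine recipients, the half-width grows by 4% to 15%; losing one of five controls adds 28%. These figures assume t-intervals with an unchanged SD, and the protocol gives no rate from which to predict the losses. A reader might infer that the response estimates will be biased in a known direction. The documents do not support that: selection of participants who stayed well is possible, but neither its direction nor its size can be derived.

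The antibiotic conflict is separate and narrow: treatment in the 14 days before Dose 2, and whether item 5 leads to exclusion from analysis.

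**What to change.** In section 6.4, replace the immunogenicity half of the sentence with a sample-level rule: results from samples taken before the interfering treatment are kept and analysed by assigned group, and only samples taken after it are set aside. Report alongside it an analysis of all available results from all dosed participants. Which of the two is primary can be settled in the statistical analysis plan; counting post-treatment samples in the main analysis is a debatable choice, and the correction does not depend on it.

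Separately, reconcile sections 5.2, 6.4 and 7.3 on antibiotics within 14 days before Dose 2, and state whether item 5 of section 6.4 leads to exclusion from analysis. Which clinical rule applies is for the sponsor.

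The cost is protocol wording, matching text in the analysis plan and one extra table. No additional samples or visits are needed.
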